**3.2.2. Describe types of data to be obtained and statistical or power analysis if indicated**

The sample size calculation is based on the assumptions that the incidence of cognitive decline at 5-7 days postoperative is 30% after on-pump surgery ^36-38^, and that one-third reduction could be achieved using RIPC. Individual patients may decline intra-hospital study follow up. We estimated loss to follow up as 5 % of the patients based on previous experience for clinical studies in our hospital. A total of 90 patients per group were estimated.

Secondary endpoints will be analysed in an exploratory way by standard statistical methods for comparing independent samples with respect to their measurement level and/or type of distribution (parametric and nonparametric methods).

With respect to feasibility of recruitment, the intended recruitment rate is based on a prospective recording of all potentially included patients from October to December 2008 in our institution. Each week a mean of eight patients fulfilling the inclusion criteria could be included. Thirty percent of these patients were estimated to give informed consent regarding study participation corresponding to two to three patients per week. Based on 52 weeks of recruitment per year and one study team (one anaesthetist, one nurse) available we calculated a realistic enrolment of 140 patients per year.

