**3.2. Methods**

**3.2.1. Describe data collection techniques.**

**3.2.1.1. Co-workers**

-> Names in brackets indicate the role of each person involved in the project

- Dr. [name] (PM), PD Dr. med. [name] (BB), PD Dr. ret. nat. [name] (MA), [name]. med. [name] (JS); Department of Anaesthesiology and Intensive Care Medicine, University Hospital Schleswig-Holstein, Campus Kiel, Germany
- Prof. [name] (JC); Department of Heart and Vascular Surgery, University Hospital Schleswig-Holstein, Campus Kiel, Germany
- Prof. [name] (KDZ); Department of Anaesthesiology and Intensive Care Medicine, University Frankfurt, Germany

**3.2.1.2. Clinical procedures (PM, BB, JS, JC):** One-hundred eighty patients undergoing cardiac surgery (single CABG, aortic- or mitral valvular surgery, combined valvular and CABG surgery, and combination of ascending aortic aneurysm surgery, valvular or CABG surgery) will be included. Thus, study population reflects a large group of patients with increased risk of perioperative morbidity and mortality. Following exclusions criteria will be defined: Emergency cases, myocardial infarction (MI) up to 7 days and stroke up to 2 months prior to enrolment, age below 18 years, off-pump heart surgery, renal failure, drug therapy with sulfonamide and nicorandil, ejection fraction less than 30%, and previous psychiatric and neurological illness. All patients will receive standard perioperative care. The applicant (PM) will inform the patient about the nature of the trial, its aims, expected advantages as well as possible risks. Each patient must consent in writing to participate in the study. The informed consent will be signed by both patient and treating investigator.

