All patients will undergo a battery of 10 neuropsychological tests 1 day before, 5-7 days and 3 months after surgery by a blinded study nurse. In accordance with the statement of consensus on assessment of neurobehavioral outcome after cardiac surgery ^31^, the battery will include tests for motor skills, verbal memory capacity, and attention. In addition, tests will be included to assess speed and capacity of working memory, visuospatial capacity, selective and sustained attention, and information processing. Cognitive decline will be defined as a decrease in an individual’s performance of at least 20% from baseline, in at least 20% of the main variables ^32^.

**3.2.1.3. Determination of biochemical plasma markers (PM, BB, MA, KDZ):** Arterial blood samples will be collected at baseline, after CPB, and after 6, 12, 24 and 48 hours after surgery. Plasma will be obtained (centrifuged at 3000g for 5 min) and stored at -20°C until assayed. In a blinded fashion, cardiac troponin I, total creatine kinase, and inflammatory biomarkers (Cytokine multiPlex for Luminex laser; Invitrogen, Karlsruhe, Germany) will be determined using the microsphere array technique (Luminex 100 system; Luminex, Austin, USA) as previously described ^33^.

**3.2.1.4. Determination of leukocyte gene expression (MA):** In a subgroup of fifty patients (n=25 of each group), exemplarily, transcriptional profiling of leukocyte gene expression before and 24 hours after surgery will be analysed by microarrays. Blood samples will be collected into PAXgene tubes for immediate mRNA stabilization and extraction. Different gene-expression pathways involving inflammation, cellular adhesion, apoptosis and stress response will be analysed ^20,34^. Experiments will be performed in collaboration with the Institute of Clinical Molecular Biology, Kiel, Germany, using an in-house research microarray according to the guidelines of the Microarray Gene Expression Data (MGED) society ^35^.

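### The 90 patients per group in section 3.2.2 do not follow from the stated 30% incidence, one-third reduction and 5% loss, and give only about a one-in-three chance of detecting that effect

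*Protocol*

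**What the plan says.** The sample size paragraph of section 3.2.2 rests on three inputs:

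- Control rate: "the incidence of cognitive decline at 5-7 days postoperative is 30% after on-pump surgery".
- Effect: "that one-third reduction could be achieved using RIPC".
- Attrition: "We estimated loss to follow up as 5 % of the patients".

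Its result is "A total of 90 patients per group were estimated". Section 3.2.1.2 (Clinical procedures) gives the matching total, "One-hundred eighty patients undergoing cardiac surgery", so 90 is the size of one arm and not of the whole trial.

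The endpoint is binary for each patient. Section 3.2.1.2 sets the rule, counted over the test variables (the quote stops one word short): "Cognitive decline will be defined as a decrease in an individual’s performance of at least 20% from baseline, in at least 20% of the main". Section 3.1.1 makes this outcome at 5-7 days the primary endpoint, and section 3.2.2 treats the secondary endpoints as exploratory. No alpha, sidedness, power, test or formula is given for the calculation.

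**The concern.** A fall from 30% to 20% is a difference of 10 percentage points between two proportions. Ninety patients per arm is far fewer than such a difference usually requires, which prompts the question whether any reasonable choice of error rates leads to 90.

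The paragraph is the protocol's only justification of the sample size, and it serves the single major hypothesis in section 3.1.3. Section 3.2.4 sends the protocol to the ethics committee and the authorities, who would take from it that 180 patients are enough to test for a one-third reduction. If they are not, the trial has a low chance of showing the effect it was set up to show, and a non-significant result could not exclude that effect.

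**Working it through.** **Inputs from the protocol.** Control rate p1 = 0.30 (section 3.2.2). Reduction by one third, so p2 = 0.30 × 2/3 = 0.20 (section 3.2.2). Loss 5% (section 3.2.2). Equal arms, 180 / 2 = 90 (sections 3.2.1.2 and 3.2.2).

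**Assumed, because not stated.** Test of two proportions with pooled variance under the null. Alpha two-sided 5%, one-sided 5% and one-sided 10%; power 70%, 80% and 90%.

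**Formula.** With p̄ = (p1 + p2)/2 = 0.25,

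n per group = [z_α √(2p̄(1−p̄)) + z_β √(p1(1−p1) + p2(1−p2))]² / (p1−p2)²

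Here √(2 × 0.25 × 0.75) = √0.375 = 0.6124 and √(0.21 + 0.16) = √0.37 = 0.6083.

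**Step 1: try to reproduce 90.** At two-sided 5% and 80% power:

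n = (1.960 × 0.6124 + 0.8416 × 0.6083)² / 0.01 = (1.2002 + 0.5119)² / 0.01 = 293.2, so 294 evaluable; 294 / 0.95 = 309.5, so 310 with loss.

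The same formula over the range of assumptions:

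| Alpha | Power | Evaluable per group | With 5% loss |
|---|---|---|---|
| two-sided 5% | 80% | 294 | 310 |
| two-sided 5% | 90% | 392 | 413 |
| one-sided 5% | 80% | 231 | 244 |
| one-sided 10% | 80% | 169 | 178 |
| one-sided 10% | 70% | 122 | 129 |

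A continuity correction only raises these (313, or 330 with loss, for the first row). Among the combinations tried, the requirement drops below 90 only at one-sided 10% with 50% power (62 evaluable, 66 with loss; 81 and 86 with continuity correction). The stated figure is therefore not reproduced under any customary choice.

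**Step 2: power of the stated size.** Evaluable per group = 90 × 0.95 = 85.5, taken as 85.

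z = [0.10 × √85 − 1.960 × 0.6124] / 0.6083 = (0.9220 − 1.2002) / 0.6083 = −0.457, so power = Φ(−0.457) = 32.4%.

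- If all 90 are evaluable: 34.0%.
- One-sided 5%, 85 evaluable: 44.4%.
- Fisher's exact test, two-sided 5%, 85 evaluable: about 27%.

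**Step 3: what 85 per group can detect.** Holding p1 = 0.30 and solving for 80% power at two-sided 5% gives p2 ≈ 0.125, a relative reduction of (0.30 − 0.125) / 0.30 ≈ 58%.

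**Step 4: the control rate at which a one-third reduction would be detectable.** With 85 per group at two-sided 5%, power is 32% at a 30% control rate, 45% at 40%, 60% at 50%, 75% at 60%, 80% at about 64% and 96% at 79%.

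**Step 5: a possible origin of 90.** For 30% versus 10%, a fall to one third rather than by one third, two-sided 5% and 90% power give 82 evaluable and 82 / 0.95 = 86.3, so 87 with loss. With continuity correction the figures are 92 and 97. These are close to 90 but not equal to it.

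**The case against.** **Alpha and power are not stated, so the calculation cannot be called wrong.** The exact requirement does depend on them, and 310 and 32% should be read as results at two-sided 5% (with 80% power for the 310). The mismatch does not depend on them: at 80% power every alpha and sidedness tried needs at least 169 evaluable per group. Reaching 80% power with 85 per group would take a one-sided alpha of about 0.25.

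**The true incidence may be higher.** Section 3.1.2 reports neurocognitive dysfunction in 30 to 79% of patients at discharge, so 30% is the bottom of the protocol's own background range, and the 64% found in step 4 lies inside that range. This stands as context: 32% is the low end of the power that the background range would allow. It does not repair section 3.2.2, which sizes the trial on 30%.

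**A reader might infer that the size was really computed for 30% versus 10%.** The near match in step 5 makes this one possible explanation, but 87 is not 90, alpha and power are free to choose, and the text says "one-third reduction could be achieved using RIPC". A one-third reduction from about 65% also needs about 87 per group with loss. The documents do not show which calculation was made.

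**A reader might infer that any significant result must overstate the effect.** That holds only if the true rates are near 30% and 20%. For a true 30% versus 10%, power with 85 per group is 91% and no overstatement need follow. At lower event rates a difference close to 10 points can be significant: 13/85 versus 4/85 is 10.6 points with p = 0.02.

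**A reader might infer that a null result will be reported as absence of protection.** Nothing in the protocol says so, and rules for reporting the result may stand in an analysis plan that is not shown.

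**Conclusion.** Section 3.2.2 is wrong as written: 90 per group does not follow from 30%, a one-third reduction and 5% loss. Under the usual two-sided 5% and 80% power the inputs need about 310 per group with loss, some 3.4 times the stated size (310 / 90); under the most lenient 80%-power variant tried they need 178, about twice it (178 / 90).

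The supported consequence is conditional. If the planned effect is the true one, a two-sided 5% test with about 85 evaluable per group misses it about two times in three (1 − 0.324 = 0.676), so a non-significant result could not exclude it. The conclusion assumes a two-proportion comparison of the binary endpoint in equal arms. How the figure of 90 arose remains unknown.

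**What to change.** Correct section 3.2.2 so that effect size and sample size agree, in one of two ways:

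- Keep 90 per group and state the effect it can detect: 30% versus about 12.5% (about 58% relative reduction) at 80% power, two-sided 5%, with 5% loss.
- Keep 90 per group and the one-third reduction, and state that about 85 evaluable per group give a power of only about 32% at two-sided 5%.

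In either case give the alpha, sidedness, power and test used. If another calculation lies behind the 90, such as a different effect or control rate, state its inputs instead.

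The cost is a change of wording with no added patients. The price is a less favourable statement: a larger required effect, or a low stated power.

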**2. Research Summary**

Cardiac surgery with cardiopulmonary bypass is associated with a predictable incidence of myocardial and neurological dysfunction due to perioperative ischaemia that accounts for significant morbidity and mortality. Cardiac surgery is further associated with a substantial systemic inflammatory response and oxidative stress contributing to multi-organ dysfunction. Remote ischaemic preconditioning (RIPC) has been demonstrated as a novel, simple, non-invasive and inexpensive intervention in which brief ischaemia of non-vital tissue protects remote organs from a sustained episode of ischaemia. The purpose of this study is to evaluate the effects of RIPC prior to cardiopulmonary bypass on the incidence and severity of perioperative ischaemic events leading to myocardial and brain dysfunction in patients undergoing complex cardiac surgery compared to control intervention. The primary endpoint is postoperative neurocognitive dysfunction. Secondary endpoints are myocardial injury assessed by Troponin I, length of stay on the intensive care unit and total hospital stay. Furthermore, we investigate underlying pathways of RIPC in modifying the perioperative stress response with respect to myocardial tissue protein expression profile.

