**Remote ischaemic preconditioning (RIPC):** The most promising clinical examples for ischaemic preconditioning are angina preceding MI or transient ischaemic attacks preceding a full stroke; these preceding sub-lethal stressors are thought to enhance the tolerance of the organ to cope with the subsequent ischaemic event. However, the clinical applicability of local ischaemic preconditioning is limited by the need to induce ischaemia in the vulnerable target organ, a process that itself may aggravate organ injury and dysfunction. A more clinically relevant stimulus represents RIPC where ischaemia of non-vital tissue might protect remote organs against ischaemia-reperfusion injury, regardless of the trigger. This powerful, innate protection is mediated by recruitment of a neuronal pathway ^12^ and various neurohumoral factors such as adenosin, opioids, bradykinine, and calcitonin gene related protein ^13-16^. During the course of previous experimental investigations, brief ischaemia of the kidney, the intestine or skeletal muscle led to reduction of subsequent MI after prolonged coronary occlusion and protection against CPB-induced neural, pulmonary and myocardial damage ^17^. In humans, it has been shown that RIPC performed by transient limb ischaemia reduces ischaemia-induced endothelial dysfunction ^18^ and decreases markers of myocardial and renal injury in patients undergoing abdominal aortic aneurysm repair ^19^. In addition, RIPC modified expression of genes coding for key proteins involved in cytokine synthesis, chemotaxis, adhesion, innate immunity signalling pathways, and apoptosis in circulating human neutrophils ^20^. Finally, Hausenloy and colleagues demonstrated in a “proof-of-principle” study that RIPC reduced troponin T release by 43% as a surrogate parameter for long-term clinical outcome in the perioperative period in patients undergoing CABG ^21^. Thus, RIPC may represent an easily accessible, novel, non-invasive and inexpensive method to potentially reduce the incidence and severity of perioperative ischaemic events such as MI, stroke and ARF.

The rationale for studying RIPC in the setting of heart surgery is based on both the considerable experimental evidence that RIPC reduces myocardial ^14^ and neuronal ^22^, as wells as a few pilot trials ^19,21,23^. However, even when RIPC has been shown to reduce infarct size ^21^, this may not necessarily translate into a readily demonstrable neurological benefit, such as reduced POCD.

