**3.1.3. Specific Aims**

**Major hypothesis:** RIPC results in less brain injury reflected by less neurocognitive dysfunction compared to control intervention after 5-7 days.

**Minor hypothesis:** RIPC results in less POCD compared to control intervention after 3 months, in less myocardial injury, better short-term outcome in terms of length of stay on the intensive care unit and total hospital stay. Further, we hypothesise that RIPC will modulate myocardial tissue protein expression profile of key proteins involved in organ protection in a subgroup of patients.

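### For troponin I, taken at baseline and five later times, the protocol names only unadjusted two-group comparisons; one baseline-adjusted summary per patient would be a low-cost gain in efficiency

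*Protocol*

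**What the plan says.** The Research Summary (section 2) lists the secondary endpoints: "Secondary endpoints are myocardial injury assessed by Troponin I, length of stay on the intensive care unit and total hospital stay". Section 3.1.3 turns this into one directional minor hypothesis, that the intervention results "in less myocardial injury, better short-term outcome in terms of length of stay on the intensive care unit and total hospital stay".

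Section 3.2.1.3 gives the sampling schedule: "Arterial blood samples will be collected at baseline, after CPB, and after 6, 12, 24 and 48 hours after surgery". That is one baseline value and five later values per patient. The list of changes dated 01/01/2009 drops several endpoints, but not troponin I.

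Section 3.2.2 gives one rule for every secondary endpoint: "Secondary endpoints will be analysed in an exploratory way", and this is to be done "by standard statistical methods for comparing independent samples with respect to their measurement level and/or type of distribution", parametric or nonparametric. It mentions no covariate, no repeated-measures model and no troponin summary. Section 3.2.3 warns that the mix of surgical procedures may make the data heterogeneous and highly variable.

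**The concern.** The rule in section 3.2.2 suits length of stay, which yields one number per patient. It suits a six-point series with a baseline less well. Two things follow.

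First, there is one hypothesis on myocardial injury, but the text does not say which troponin quantity tests it. An analyst may compare the arms at each of five times and stress the time that looks best.

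Second, the class of method named is an unadjusted two-sample comparison. The baseline sample is already collected and the procedure is known for every patient, yet neither has a stated role. If either predicts troponin release, precision is given away in a population that the protocol itself expects to be variable.

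At stake is how clearly and how precisely a secondary endpoint is answered. The primary endpoint is not affected.

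**Working it through.** **Inputs from the protocol.** Six samples per patient, five of them after baseline (3.2.1.3); 90 patients per group and 5% loss (3.2.2), so 90 x 0.95 = 85.5, taken as 85 evaluable per arm. The protocol gives no figure of its own for troponin I: no SD, no correlation, no target difference. The 90 per group was derived for cognitive decline and serves here only as the arm size. (It is not reproduced from its own inputs: 30% against 20%, two-sided 5% and 80% power, gives 294 per group before loss. That is a separate matter, and this point does not depend on it.)

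**Assumed.** Two-sided 5% level and 80% power; correlation r between post-baseline values, 0.3 to 0.9, equal for all pairs; correlation rho between baseline and the chosen summary, 0 to 0.7.

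**Step 1: five separate tests.** If independent, the chance of at least one false positive is 1 - 0.95^5 = 0.226. Values from the same patient are correlated, so the true figure is lower. Simulating five equally correlated normal test statistics (400,000 draws, two-sided 5% each) gives the second column below.

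**Step 2: one summary.** A single prespecified summary has a false-positive chance of 5%. Taking the plain mean of the five values as a stand-in for an area under the curve, its variance relative to one value is (1 + 4r)/5; the square root gives the relative standard error.

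| r | At least one false positive, five tests | SE of mean of five relative to one value |
|---|---|---|
| 0.3 | 20.7% | 0.66 |
| 0.5 | 18.3% | 0.77 |
| 0.7 | 14.8% | 0.87 |
| 0.9 | 10.2% | 0.96 |

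**Step 3: baseline adjustment of that summary.** ANCOVA multiplies the residual variance by 1 - rho^2 and the standard error by its square root. The unadjusted detectable difference with 85 per arm is (1.960 + 0.842) x sqrt(2/85) = 0.43 SD.

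| rho | Variance factor | Cut in SE | Detectable difference (SD) |
|---|---|---|---|
| 0 | 1.00 | 0% | 0.43 |
| 0.1 | 0.99 | 0.5% | 0.43 |
| 0.3 | 0.91 | 4.6% | 0.41 |
| 0.5 | 0.75 | 13.4% | 0.37 |
| 0.7 | 0.51 | 28.6% | 0.31 |

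Procedure class acts in the same way, with the share of variance explained by all covariates together in place of rho^2. If the covariates explain nothing, the price is a few degrees of freedom out of 85 + 85 - 2 = 168, which is negligible.

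**Step 4: a change score instead.** A change from baseline, compared by a two-sample test, would stay within the stated class of methods. With equal SDs before and after, its variance factor is 2(1 - rho): 1.40 at rho 0.3, 1.00 at 0.5 and 0.60 at 0.7. ANCOVA gives 0.91, 0.75 and 0.51. The change score therefore does not remove the case for ANCOVA.

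**The case against.** The strongest reply concerns wording. Independent samples means the two randomised arms, which are independent. A reader might infer that the plan treats serial values in one patient as independent, or commits itself to five tests. The text says neither. A t-test or Mann-Whitney test on one peak or area per patient is an independent-sample method, is valid, and deals with the repetition. This stands.

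The analysis is labelled exploratory, so a familywise error rate carries limited weight. This also stands; the rate describes the room for selective emphasis, not a broken confirmatory claim.

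The precision gain rests on assumed correlations. A reader might infer that baseline must matter because infarctions more than 7 days old are allowed. No document supports that. The exclusion of "myocardial infarction (MI) up to 7 days and stroke up to 2 months prior to enrolment", together with emergency cases and renal failure, may equally narrow the baseline spread and leave little to gain. An unadjusted comparison of randomised arms is also unbiased.

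Finally, the choice of summary and covariates often belongs in a statistical analysis plan, which is not shown, and the numbered list of key secondary endpoints (3.1.1) has no visible item 5, so a troponin definition may have been lost from the text. Failure to define the summary therefore cannot be held against the protocol. What remains is narrower: section 3.2.2 does name a class of method for these endpoints, and a better one is available from data already collected.

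**Conclusion.** The point holds as an efficiency improvement for a secondary endpoint. The protocol names only unadjusted two-group comparisons for a marker with a baseline and five later values. It leaves time-by-time testing open without requiring it.

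If the times were tested separately, the chance of at least one false positive would be about 10% to 21% (r from 0.9 to 0.3). The 23% figure needs independent tests and should not be quoted as the expected size. The variance reduction from baseline adjustment is nil at rho 0, 9% at 0.3 and 25% at 0.5, all assumed. If baseline turns out to be weakly informative, most of the benefit will come from having one summary, with any further gain from procedure class.

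It would go too far to say that the stated method is invalid, that it biases the troponin result, or that adjustment is certain to sharpen it.

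**What to change.** In section 3.2.2, give troponin I its own sentence: one summary per patient, for example log area under the curve from end of bypass to 48 hours, compared between arms by ANCOVA with baseline troponin (on the log scale) and procedure class as covariates. Show the individual times descriptively, without separate tests. A single release measure would also match the background, which reports the earlier bypass-grafting study by one figure ("RIPC reduced troponin T release by 43" per cent).

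Three short additions make this workable: state that the baseline sample is drawn before cuff inflation, give a rule for missed samples within the area under the curve, and give a rule for values below the detection limit before taking logs. Other single summaries, such as the peak, are defensible; what matters is to name one in advance and adjust it.

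The cost is analysis wording only. No extra patients, samples or assays are needed, and the exploratory label can stay.
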